## Abstract

**Background:**

Despite the significant health benefits of regular physical activity, approximately half of American adults, particularly women and minorities, do not meet the current physical activity recommendations. Mobile phone technologies are readily available, easily accessible and may provide a potentially powerful tool for delivering physical activity interventions. However, we need to understand how to effectively apply these mobile technologies to increase and maintain physical activity in physically inactive women. The purpose of this paper is to describe the study design and protocol of the mPED (**m**obile phone based **p**hysical activity **ed**ucation) randomized controlled clinical trial that examines the efficacy of a 3-month mobile phone and pedometer based physical activity intervention and compares two different 6-month maintenance interventions.

**Methods:**

A randomized controlled trial (RCT) with three arms; 1) PLUS (3-month mobile phone and pedometer based physical activity intervention and 6-month mobile phone diary maintenance intervention), 2) REGULAR (3-month mobile phone and pedometer based physical activity intervention and 6-month pedometer maintenance intervention), and 3) CONTROL (pedometer only, but no intervention will be conducted). A total of 192 physically inactive women who meet all inclusion criteria and successfully complete a 3-week run-in will be randomized into one of the three groups. The mobile phone serves as a means of delivering the physical activity intervention, setting individualized weekly physical activity goals, and providing self-monitoring (activity diary), immediate feedback and social support. The mobile phone also functions as a tool for communication and real-time data capture. The primary outcome is objectively measured physical activity.

**Discussion:**

If efficacy of the intervention with a mobile phone is demonstrated, the results of this RCT will be able to provide new insights for current behavioral sciences and mHealth.

**Trial Registration:**

ClinicalTrials.gov#:NCTO1280812

## Background

Physical inactivity is associated with an increase in cardiovascular disease, Type II diabetes, hypertension, certain types of cancer, and obesity [1-3]. The National Physical Activity Guidelines recommend at least 150 minutes a week of moderate-intensity physical activity [4]. However, approximately half of American adults, particularly women and minorities, do not meet this recommended physical activity recommendation [5].

Mobile communication technologies are widely available; the majority of adults in the United States own a mobile phone [6]. Mobile phones have the advantage of being portable and easily accessible. These are qualities that make them powerful tools for delivering physical activity interventions. Despite this considerable potential, the majority of mobile phone based physical activity intervention studies have had a relatively small sample size, have evaluated only the short-term effects of the intervention, and have been conducted without a proper control group [7-9]. Thus, it is important to systematically investigate whether mobile phone interventions work effectively, and over what period of time.

In order to better understand the feasibility and acceptability of a mobile phone based physical activity intervention, we conducted a three week pilot study on physically inactive women in the San Francisco Bay Area. The results of both quantitative and qualitative analyses of this pilot study have been published elsewhere [8,10,11]. In the pilot study, sedentary women wore a pedometer and were issued a mobile phone loaded with a custom-designed physical activity mobile phone application. In summary, this pilot study had a relatively high adherence rate for use of all components of the intervention; the pedometer, physical activity diary and response to daily messages. In addition, the women in the pilot study significantly increased their objectively measured steps over the three week observation period [8].

After completion of the pilot study, some improvements were made to the mobile application in order to prepare for a full-scale randomized control clinical trial intended to test the efficacy of the mobile phone based physical activity intervention among sedentary women. The final usability test was further conducted with six women who were unfamiliar with the proposed study prior to launching a full-scale randomized controlled clinical trial (RCT) of our **m**obile phone based **p**hysical activity **ed**ucation (mPED) program.

### Study aims

The aims of this RCT are threefold: 1) to assess the efficacy of the 3-month mobile phone and pedometer based physical activity intervention on increasing physical activity compared to the control group; 2) to compare the efficacy of the 6-month maintenance intervention-PLUS to the 6-month maintenance intervention-REGULAR; and 3) to explore the role of potential mediating factors (self-efficacy for physical activity, social support, and barriers for physical activity) and moderating factors (body mass index and age) on changes in outcomes at 3, 5, 7 and 9 months. The primary outcome measure for the first two aims is the total steps per day as measured by the Omron Active Style Pro HJA-350IT (triaxial accelerometer) pedometer.

## Methods

### Study design

This is a randomized controlled clinical trial with three arms; 1) PLUS (3-month mobile phone and pedometer based physical activity intervention and 6-month mobile phone diary maintenance intervention), 2) REGULAR (3-month mobile phone and pedometer based physical activity intervention and 6-month pedometer maintenance intervention), and 3) CONTROL (pedometer only, no intervention will be provided). All groups receive a pedometer to use for nine months. (See Figure 1)

**Figure 1 F1:**
[figure not shown]
**Flow of the study design**. ^0) ^3-week run-in: To be randomized, participants must successfully complete a 3-week run-in period (defined as at least 80% adherence rate in using daily message and diary and at least eight hours a day for ≥ 80% of the run-in period and completed a fasting blood test in a research lab). ^1) ^CONTROL: Pedometer only for 9-months, no physical activity intervention, ^2) ^REGULAR: 3-month mobile phone and pedometer based physical activity intervention and 6-month pedometer maintenance intervention, and ^3) ^PLUS: 3-month mobile phone and pedometer based physical activity intervention and 6-month mobile phone diary maintenance intervention.

### Ethical approval

The study protocol including informed consent form, study questionnaires, educational and recruitment materials has approved by the University of California, San Francisco Committee on Human Research (Institutional Review Board) and the Data and Safety Monitoring Board (DSMB). All potential participants will receive a copy of the informed consent electronically or by mail after successful completion of the telephone screening. This consent will be reviewed and signed in the research office before enrollment in the study.

### Participants

A total of 192 physically inactive women who meet all inclusion criteria and successfully complete a 3-week run-in period will be randomized into one of the three groups. Physically inactive women will be recruited from the San Francisco Bay Area through the use of local newspaper advertisements, Craigslist (a classified advertisement website), Facebook, and flyers posted at local hospitals, medical clinics, dental clinics, community centers, and supermarkets, with the intent of recruiting a diverse and representative sample.

### Inclusion/Exclusion criteria

Inclusion criteria are: 1) sedentary lifestyle at work and/or during leisure time, as assessed using the Stanford Brief Physical Activity Recall Survey [12], Physical Activity History Questionnaire [13] and baseline average daily steps measured during the run-in period; 2) intent to be physically active; 3) female, age 25 - 69; 4) access to a home telephone or a mobile phone; 5) speak and read English; and 6) body mass index (BMI) between 18.5 - 43.0 kg/m^2^. The exclusion criteria are: 1) known medical conditions or other physical problems that need special attention in an exercise program (e.g., history of myocardial infarction, angioplasty, or angina, admission to the hospital for evaluation of chest pain, use of nitroglycerin to treat angina, uncontrolled hypertension, diabetes mellitus with insulin treatment, osteoporosis, or under active treatment for cancer); 2) planning an international trip during the next four months (subjects are required to upload mobile phone data to a server daily, and will not be able to do so from abroad); 3) pregnant/delivered a baby during the past six months; 4) known severe hearing or speech problem; 5) history of eating disorder (e.g. binge eating disorder, bulimia nervosa, anorexia nervosa); 6) in recovery from substance abuse; 7) currently participating in lifestyle modification programs or research studies that may potentially confound the results of the study; and 8) history of bariatric surgery or plans for bariatric surgery in the next twelve months. We will not exclude women who have never used a mobile phone or are not current mobile phone users.

### Screening/Baseline visit and run-in period

All potential subjects will be screened by telephone and eligible subjects will be invited to attend a screening/baseline visit. After obtaining a written informed consent, baseline data will be gathered to determine eligibility. Eligible participants will be issued a mobile phone and pedometer; training will be provided to insure participants can successfully use both devices. During the 3-week run-in, the pedometer will be set to record and store physical activity (e.g. steps), but no display of steps will be visible (only date and time will be visible) on the pedometer. A run-in mobile phone application has been created specifically for this phase of the study; it is designed to mimic the intervention application without any content to encourage or support increasing physical activity.

The run-in period has two purposes: 1) to determine the baseline average daily steps and 2) to determine if the participant will be able to comply with the requirements of the study. In order to be eligible for randomization, participants must successfully complete a fasting blood test at a research lab in addition to completing the run-in period with at least an 80% adherence rate in each of the following: 1) daily message responses, 2) daily activity diary responses, and 3) pedometer wearing time of at least 8 hours per day.

### Randomization

One hundred and ninety-two women will be randomly assigned in a 1:1:1 ratio to the PLUS, REGULAR or CONTROL groups. Permuted-blocked randomization will be used to ensure that the number of participants in the three treatment groups is close to our goal of an exact 1:1:1 ratio. Block size will vary randomly from three to nine in a schedule that is not known to investigators and research staff. The data management staff will prepare a set of sealed, opaque envelopes, numbered consecutively, and containing the study group assignment.

### Blinding

Due to the nature of the mobile phone intervention, blinding the participant, research staff, and investigator is not possible. In order to minimize expectation bias, participants are informed only that we are testing two different physical activity interventions (pedometer intervention versus pedometer plus mobile phone application intervention). Participants who are randomized into the PLUS and REGULAR groups are blinded to their maintenance intervention (PLUS or REGULAR) assignment until they complete the 3-month mobile phone and pedometer based intervention.

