### Physical activity interventions

The physical activity interventions were designed based on the Social Cognitive Theory [14]. There are two components to the physical activity intervention: 1) a brief face-to-face physical activity intervention, and 2) the 3-month mobile phone and pedometer based physical activity intervention. All women randomized into the PLUS and REGULAR groups will receive the 3-month mobile phone and pedometer physical activity intervention in an identical fashion.

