#### Brief face-to-face brief intervention

Upon randomization into a 3-month mobile phone and pedometer physical activity intervention group, each woman in the PLUS and REGULAR groups will be given a face-to-face interactive session by trained research staff. The face-to-face intervention is a structured interview containing seven domains: 1) overview of the physical activity program and tailored short and long-term goal setting; 2) education about duration and intensity of brisk walking and the health benefits of exercise; 3) identification of barriers to increasing physical activity and development of strategies to overcome these barriers; 4) value and identification of social support while increasing physical activity; 5) relapse prevention; 6) education about healthy diet and weight maintenance; and 7) physical activity safety. The face-to-face intervention is designed to be interactive and actively elicits the participant's participation. An individualized written physical activity plan will be developed during the face-to-face intervention. The trained research staff will revisit and revise the plan at the 1.5- and 3-month visits.

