### Physical activity maintenance

There are two different 6-month maintenance interventions, REGULAR (pedometer only) and PLUS (pedometer plus mobile phone physical activity diary). A 6-month maintenance period follows the 3-month mobile phone and pedometer based physical activity intervention; participants will be randomly assigned to one of two different maintenance interventions at the randomization visit. The maintenance intervention-REGULAR group will use the pedometer daily and the maintenance intervention-PLUS will use the pedometer and physical activity mobile phone diary daily. The purpose of the two different maintenance intervention groups is to gain insight into the "dose-response" to self-monitoring and feedback. In other words, is keeping a mobile phone diary and pedometer for 6-months a better physical activity maintenance method than a pedometer alone? The subjects in the control group continue using a pedometer for these six months of the study. The subjects in all three groups will be asked to bring back the pedometer to a research office to download the pedometer data at 5, 7 and 9 months. At the 9-month visit, participants will return all pedometers and study mobile phones (if there is any) to the research office. All participants will receive a follow-up telephone call at 12 months to assess their level of physical activity using the 7-Day Physical Activity Recall Questionnaire.

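### The statement that staff cannot be blinded is too broad: PLUS versus REGULAR could be kept from them until month 3, and nothing in the article does so

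*Protocol article*

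**What the plan says.** All places are in the Methods of the protocol article.

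- **Blinding:** "Due to the nature of the mobile phone intervention, blinding the participant, research staff, and investigator is not possible". The same section then says that women in PLUS and REGULAR "are blinded to their maintenance intervention (PLUS or REGULAR) assignment until they complete the 3-month mobile phone and pedometer based intervention". It makes no matching provision for staff or investigators.
- **Randomization:** "One hundred and ninety-two women will be randomly assigned in a 1:1:1 ratio to the PLUS, REGULAR or CONTROL groups". On concealment: "The data management staff will prepare a set of sealed, opaque envelopes, numbered consecutively, and containing the study group assignment".
- **Physical activity maintenance:** "participants will be randomly assigned to one of two different maintenance interventions at the randomization visit".
- **Physical activity interventions:** women in PLUS and REGULAR "will receive the 3-month mobile phone and pedometer physical activity intervention in an identical fashion".
- **Brief face-to-face brief intervention:** trained research staff hold an interactive session after randomization. It covers seven domains, including tailored goals, barriers and relapse prevention, and yields an individual written plan. "The trained research staff will revisit and revise the plan at the 1.5- and 3-month visits".

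**The concern.** The reason given for not blinding staff is the nature of the intervention. For three months that reason does not separate PLUS from REGULAR, because nothing the women receive differs. The maintenance arm is nevertheless fixed at the start, about three months before it is needed, and the text protects only the participant from knowing it.

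Aim 2 compares the two maintenance programmes on steps per day. If a counsellor knows which women will later stop using the diary, she may, without intending to, spend more effort on relapse prevention or shape the written plan differently. The women's own masking would also depend on staff not revealing what they know. Either would introduce a PLUS-REGULAR difference that is not due to the maintenance programme, in a comparison where the masking is available at almost no cost.

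**Working it through.** The article states no figure on this point, so the main check is to set the sections side by side.

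**1. Where the stated reason applies**

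| Comparison and period | Does treatment differ? | Does the reason hold? |
|---|---|---|
| Intervention vs CONTROL, any time | Yes (session, app, messages) | Yes |
| PLUS vs REGULAR, after month 3 | Yes (phone diary or none) | Yes |
| PLUS vs REGULAR, months 0 to 3 | No (Physical activity interventions) | No |

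The Blinding section confirms the last row, since it masks the women to this split over the same period. If those who receive the treatment can be masked, so can those who deliver it.

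**2. Could staff know the arm?** Allocation is a single 1:1:1 step to three named groups, the envelopes are described as "containing the study group assignment", and the maintenance arm is assigned at the randomization visit. No second envelope or delayed disclosure is described, and only participants are masked. The natural reading is that staff may know. It remains an inference, because the article does not say who opens the envelope or what the counsellor sees.

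**3. Who is exposed, and when.** 192 × 2/3 = 128 women are in PLUS or REGULAR. Two staff contacts clearly precede disclosure: the session after randomization and the 1.5-month plan revision. The 3-month revision may come before or after it, because the women's masking ends when they complete the 3-month programme.

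**4. What could be told apart.** Both arms use the diary through month 3, and daily steps are stored by the device. A PLUS-REGULAR difference at month 3 would therefore be visible and could not be a diary effect. A difference that emerges only afterwards, such as from stronger relapse-prevention advice to one arm, would coincide with the maintenance contrast and could not be separated from it.

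**5. Scale, for illustration only.** Sample size and power gives 90% power for 1100 steps/day with 114 women, or 57 per arm. Two-sided alpha of 0.05 is assumed here because the article gives none.

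- Implied standard error of the contrast: 1100 / (1.960 + 1.282) = about 339 steps/day.
- At the 64 per arm actually planned: 339 × √(57/64) = about 320.
- Type I error under a bias *b*: P(|Z + b/SE| > 1.96).

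| Assumed *b* (steps/day) | Share of 1100 | SE 339 | SE 320 |
|---|---|---|---|
| 0 | 0% | 0.050 | 0.050 |
| 100 | 9% | 0.060 | 0.061 |
| 200 | 18% | 0.091 | 0.096 |
| 300 | 27% | 0.143 | 0.155 |

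The values of *b* are assumptions with no source in the article. The table shows how sensitive the test would be, not how large a bias to expect. A bias in the opposite direction would hide a real effect.

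**The case against.** The best case for the plan has three parts.

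**Staff knowledge is not stated.** Assignment is not disclosure. The women are kept unaware until month 3, so some means of withholding the arm must exist. The statistical section also speaks of characteristics measured before each randomization, which might suggest a staged process. Envelope handling is a detail that a condensed article may leave to the full protocol. It is right that the article does not establish that staff know the arm. But it does not simply leave the matter open: it says staff cannot be blinded, and for this split and period the reason given does not apply. The hint of more than one randomization does not fit the single allocation described elsewhere and should be reconciled.

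**The room for bias is small.** The session is a structured interview with the same seven domains for all intervention women. Daily messages are pre-programmed, weekly step goals are calculated from baseline, and the primary outcome is downloaded from a device. This stands and limits the risk. It does not remove it: the session is interactive, the plan is individual, and objective measurement does not correct for differently delivered counselling.

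**Later disclosure has a price.** A plan revised at 3 months before the arm is known cannot take account of whether the woman keeps the diary. This also stands, and the fix allows for it.

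A reader might also infer three stronger things that the documents do not support: that a month-3 difference could be mistaken for a diary effect (both arms have the diary until then); that withdrawals would be handled differently by arm (nothing suggests it); and that all three staff contacts precede disclosure (only two clearly do).

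**Conclusion.** The point holds as a flaw in the blinding statement and a missed safeguard. The claim that staff and investigators cannot be blinded is wrong for PLUS versus REGULAR in months 0 to 3. As written, the staff who counsel about 128 women at randomization and at 1.5 months may know the future maintenance arm. This opens a route to differential counselling and to accidental unmasking before the Aim 2 comparison.

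The conclusion rests on the natural reading that one three-way assignment is opened at the randomization visit. The size of any bias is unknown, and existing safeguards limit it. The part that could not be recovered in analysis is a delayed effect of different counselling. The intervention-versus-CONTROL comparison in Aim 1 is not affected. This is a cheap and worthwhile improvement, not a defect that invalidates the design.

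**What to change.** 1. Keep the 1:1:1 schedule as it is, but disclose it in two steps. At the randomization visit the envelope shows only 'intervention' or 'CONTROL'. For intervention women, data management, who already prepare the envelopes, hold the PLUS/REGULAR assignment sealed until the 3-month pedometer download and questionnaires are complete.
2. Replace the first sentence of the Blinding section with text to this effect: participants, staff and investigators are masked to PLUS versus REGULAR until 3-month data collection is complete; masking is not possible for intervention versus CONTROL, nor for PLUS versus REGULAR after that disclosure.
3. Reconcile the wording in the statistical section that implies more than one randomization with the single allocation described under Randomization.

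**Cost:** a second set of about 128 envelopes and a line in the visit procedure. Maintenance instructions, and any plan revision that depends on the arm, must follow the 3-month data collection. Sample size, allocation ratio, visits and treatment are unchanged.
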